**Figure 1 F1:**
[figure not shown]
**The minimum and maximum distances between intervention and control groups are 1.5 and 5 kilometers, respectively**. Map of areas of control (C) and intervention (I) groups.

A total of 5630 subjects under coverage of one of the three health centers which is far from two other centers (Figure 1), were considered for lifestyle modification using primary, secondary and tertiary preventions for NCD.

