### Schools

The School-based lifestyle modification subprogram is designed as a multidisciplinary health promotion program using a population approach that is underpinned by the Health Promoting Schools philosophy. All strategies are focused on adolescents aged 12 to 18 years. The program targets the whole school community including parents, students, staff, teachers and the school environment. It is intended to influence anti-tobacco practice and not simply knowledge in the schoolchildren. We selected those schools that had more distance from another area, in both control and intervention areas. The interference of students attended in schools in intervention and control areas is less than 8%

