### Biostatistical considerations

#### Sample size

For baseline data collection, based on predicted prevalence rates of 30% for dyslipidemia in people <30 and 45% for those ≥ 30 years of age, confidence interval of 95%, study power of 80%, attrition rate of 20%, design effect of 2% for seven age groups and two sexes, sample size was calculated to be 14280. Therefore, 15005 subjects were selected randomly from areas covered by 3 health centers. In phase 2 of TLGS, based on 5% decrease in serum cholesterol, two gender, three age groups, 5% design effect and 30% attrition rate, sample size for intervention group was calculated as 4750 subjects. Therefore, population covered by one of the 3 health centers (5630 people) selected for intervention and 9375 subjects under coverage of other two centers used as controls.

Because of the wide scope of the project and variety of the measured variables, different types of analyses are performed, depending on the type of the reports or the variables and outcomes.

Although the original of this study was based on reducing hypercholesterolemia, however, in all subjects including those less healthy or normals, changes in other risk factors, NCD, and outcomes delineated in this study will also be followed in statistical considerations.

In most of analyses we will considered each individual separately, however, for interfamilial relations we will consider intraclass correlations in analyses. It should be also mentioned that in multistage cluster random sampling procedure, each health center in district 13 was a cluster and families in three randomly selected centers were recruited. Continuous data are expressed as their measures of location and spread in total and subgroups. For qualitative and categorized continuous variables, percentages and frequency distributions are reported.

Normality of distribution of the continuous variables will be examined using histograms, measures of skewness and kurtosis, Kolmogrove-Smirnove test and sometimes Chi-square test. When log-transformed values are used, geometric means are computed. Percentiles will be used to describe the high or low values of the skewed variables. When assumptions of the parametric statistical methods are not met, nonparametric methods of their counterparts will be used. These methods also were used for analysis of variables, not originally continuous, such as attitudes, quality of life etc.

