Incidence rates of NCDs such as diabetes mellitus, angina pectoris, myocardial infarction, hypertension etc., will be estimated adjusted mainly for age and sex. Relative risks for different factors and their 95% confidence interval will be reported.

Continuous variables will be compared between intervention and control groups using student's t-test. Analysis of variance (ANOVA) will be used to compare the variables among three or more subgroups followed by appropriate post hoc test such as Tukey. To adjust the comparison by the potential confounding variables, two or three-way ANOVA will be used. In addition, analysis of covariance will be employed when adjusting for a covariate correlated with the dependent variable. To compare the proportions between two or more groups, Chi-square test of independence and Fisher exact test will be employed. Matel-Haenszel test will be used when adjustment required. To compare the data with their baseline, paired t-test and repeated measures analysis of variance or McNemar, Sign and Friedman tests will be used.

To evaluate the relationship between variables, Pearson or Spearman correlation coefficients is used Multiple regression analysis will be used to find out the relationship between variables such as blood pressure, fasting blood sugar, lipid profiles and variables regarded as independent variables such as body mass index, waist circumference, lipid profiles, age, etc.

When the outcome variable was defined as dichotomous, for instance, diabetes mellitus, hypertension, etc., multiple logistic regressions was employed to assess the relation of potential risk factors and the outcomes. Multinomial logistic regression will be used when the outcome is defined as polychromous variable, e.g., diabetes mellitus, impaired glucose tolerance (IGT) and normal. Odds ratio and its confidence interval will be reported and interpreted. Secondary outcomes (e.g., mortality, cardiovascular morbidity) will be analyzed using life table method to evaluate the association of different factors on survival time, Cox regression analysis was performed. A proportional hazards regression model will be used to evaluate potential covariability that may modify the primary and secondary outcomes. The adequacy of the models will be checked, usually, using the Hosmer-Lemeshaw statistic. In addition, ROC curve and its area under curve (AUC) will be used to compare the predictability of different fitted models.

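### One intervention centre is compared with two control centres combined, by an individual-level test with no centre-level contrast, so the stated error bars leave out drift between areas

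*Protocol article*

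**What the plan says.** All references are to the protocol article.

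- **Groups.** Sample size, under Biostatistical considerations, has the "population covered by one of the 3 health centers (5630 people) selected for intervention" and the "9375 subjects under coverage of other two centers used as controls". Table 3 likewise shows a single control column.
- **Clusters.** The same section states that "each health center in district 13 was a cluster and families in three randomly selected centers were recruited".
- **Unit of analysis.** "In most of analyses we will considered each individual separately, however, for interfamilial relations we will consider intraclass correlations in analyses".
- **Test.** "Continuous variables will be compared between intervention and control groups using student's t-test". ANOVA, analysis of covariance, Mantel-Haenszel and regression methods are also named. None is given a centre term.
- **Choice of the intervention centre.** Study population describes it as "one of the three health centers which is far from two other centers". No random allocation among the three centres is described.
- **Separation of areas.** The Figure 1 caption says: "The minimum and maximum distances between intervention and control groups are 1.5 and 5 kilometers, respectively". On pupils, Schools says: "The interference of students attended in schools in intervention and control areas is less than 8" per cent.

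**The concern.** With one intervention centre, area and intervention coincide. If cholesterol, blood pressure or smoking moves differently in that part of the district for any other reason, a two-group test on individuals credits the difference to the intervention. Adjusting individuals for age, sex or other covariates does not remove a trend that belongs to the area. Allowing for family correlation does not either, because families lie within centres.

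The two control centres are the only areas observed under the same condition. The difference between their changes is the design's one direct sight of how far untreated areas drift apart, and no stated analysis shows it. If some of the intervention reached one control area, the combined control group would dilute the effect without revealing it.

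The abstract concludes that this controlled intervention will test prevention in the community. That claim rests on this single contrast, whose stated precision reflects thousands of individuals rather than three areas.

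**Working it through.** **The plan's own figure.** The article gives 4750 as the calculated size of the intervention group. It cannot be reproduced, because the mean and SD of cholesterol and the phase 2 alpha and power are not given. The point does not depend on it.

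**Inputs.**
- From Sample size: 5630 intervention, 9375 control, 30% attrition. The attrition figure is stated for the intervention group; applying it to both groups is an assumption.
- Retained: 5630 × 0.7 = 3941 and 9375 × 0.7 = 6562.5.
- Assumed: SD of individual cholesterol change 35-45 mg/dl; SD of true area-level change (tau) 0.5, 1 or 2 mg/dl; two control centres of equal size. The article gives none of these.

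**Step 1. Standard error of the stated comparison.**
SE_naive = SD × √(1/3941 + 1/6562.5) = SD × 0.02015, which is 0.705 for SD 35 and 0.907 for SD 45.

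**Step 2. Standard error with area drift.** One area against the mean of two adds tau² × (1 + 1/2):
SE_true = √(SE_naive² + 1.5 × tau²).

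**Step 3. Rejection rate of the nominal 5% test under no effect.**
Rate = 2 × [1 − Φ(1.96 × SE_naive / SE_true)].

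| tau (mg/dl) | SE_true, SD 35 | Rate, SD 35 | SE_true, SD 45 | Rate, SD 45 |
|---|---|---|---|---|
| 0.5 | 0.934 | 13.9% | 1.094 | 10.4% |
| 1 | 1.413 | 32.8% | 1.524 | 24.3% |
| 2 | 2.549 | 58.8% | 2.612 | 49.6% |

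As intraclass correlations of change by centre, tau²/(tau² + SD²), these run only from 0.25/(0.25 + 2025) ≈ 0.0001 to 4/(4 + 1225) ≈ 0.003. Starting instead from assumed correlations of 0.0005 to 0.01 gives rates of about 25% to 75%.

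**Step 4. How much the control-control contrast can do.** It carries one degree of freedom, for which the two-sided 5% critical value of t is 12.7. A 95% interval for the effect built on it would have a half-width of 12.7 × √1.5 / √2 ≈ 11 times the observed control-control difference. It can expose drift but cannot supply a usable formal test.

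**Step 5. Could it serve as a decision rule?** Take the rule that both intervention contrasts agree in direction and both exceed the control-control difference. Simulated under no effect with the sizes above, it is met in about 32-33% of cases for tau from 0 to 4 mg/dl. When drift dominates, symmetry explains this: the intervention centre is the extreme one of three with probability 2/3, and its gap to the nearest centre exceeds the control-control gap half the time, giving 1/3. Added to the nominal 5% test, the rule still leaves about 16-20% false claims at tau = 1 and 26-28% at tau = 2.

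**Step 6. Spillover.** If one of two equal control areas receives a fraction f of the effect, the combined contrast shows 1 − f/2 of it: 87.5% for f = 0.25, 75% for 0.5 and 50% for 1. These fractions are illustrative.

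**The case against.** The strongest reply is that the sentence on controls sits in a sample-size paragraph of a condensed article and only says who the controls are. Centre is known for everyone, the article says analyses vary with the report and outcome, and results by centre could appear in an analysis plan that is not shown. Part of this stands: a reader might infer that centre information is thrown away, and the article does not say so. But the article does fix the groups, the test, the individual as the usual unit and the family as the level for intraclass correlation. Followed as written, that method gives error bars without between-centre variation. That is a stated choice rather than a missing detail.

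Three other stronger readings are tempting and not supported.

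- *Every named comparison has two groups.* The article also names ANOVA for three or more subgroups and other methods that could carry a centre term. It does not assign them to centre.
- *One control area is nearer and contaminated.* The caption gives a range of distances between groups, the map is not shown, and the intervention centre is described as far from both others. The school figure is also a partial safeguard, since schools were chosen for their distance from the other area.
- *Separating the controls would show that the intervention area had no trend of its own.* With one degree of freedom it cannot. The root limitation is a single intervention cluster, which separate reporting exposes but does not cure.

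It is also fair to object that the error rates depend on assumed SDs. They are ranges, not estimates.

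**Conclusion.** The concern holds as a defect in the stated comparison and in what may be concluded from it. The article recognises centres as clusters, then compares one centre with two combined on individuals and states no contrast that would show area drift. Under the assumptions in the working, the nominal 5% test rejects under no effect about 10-14%, 24-33% or 50-59% of the time for area SDs of 0.5, 1 or 2 mg/dl. The document gives neither SD, so the size is conditional, but small drift is enough to matter at these sample sizes. This should be fixed. It is not a must-fix point, because the data for reporting by centre remain available and such reporting cannot by itself repair a one-centre intervention arm.

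**What to change.** 1. Beside the stated comparison of change from phase I, report three contrasts: intervention v control centre 1, intervention v control centre 2, and control centre 1 v control centre 2. Label the last a descriptive benchmark of area drift and possible spillover.
2. Do not let the rule that both intervention contrasts exceed the control-control difference suffice for claiming an effect.
3. State that p-values and intervals from the combined individual-level comparison do not include between-centre variation, and that one intervention centre cannot separate the intervention's effect from that area's own trend.
4. Limit the conclusion accordingly, above all where the intervention-control differences are not clearly larger than the control-control difference.

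The cost is analysis and reporting wording only. Study population shows that families and their postal addresses were drawn from the centres' own files, so no new data are needed. The downside is more contrasts to report and a more cautious claim.

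### One health centre is compared with two, but the named between-group tests treat people as independent, so their p-values and intervals contain no centre-level variation

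*Protocol article*

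**What the plan says.** Under Biostatistical considerations (Sample size), the protocol article has the "population covered by one of the 3 health centers (5630 people) selected for intervention" and the "9375 subjects under coverage of other two centers used as controls". The text below Figure 1 (Study population) identifies the intervention centre as "one of the three health centers which is far from two other centers", and Lifestyle interventions again gives distance from the control areas as part of the rationale. No random allocation of centres to arms is described.

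The Sample size section also says that "each health center in district 13 was a cluster and families in three randomly selected centers were recruited". The same paragraph sets the unit of analysis: "In most of analyses we will considered each individual separately". The one allowance for correlation is at family level: "for interfamilial relations we will consider intraclass correlations in analyses".

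Further on in the biostatistics text: "Continuous variables will be compared between intervention and control groups using student's t-test". ANOVA, ANCOVA, chi-square, Fisher and Mantel-Haenszel methods are named as well. None is given a centre term.

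**The concern.** The unit assigned is the health centre, and there are three of them. A test on individuals asks whether the people of one centre differ from the people of two others by more than person-to-person variation explains. It does not ask whether the difference exceeds what separates centres without any intervention.

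Centres can drift apart over a follow-up of at least 20 years because of local services, population turnover or economic change. With a single intervention centre, such drift cannot be told apart from an intervention effect, and the planned standard error leaves it out. Much of the programme also reaches people in groups (schools, religious meetings, newsletters, volunteers), so outcomes within an area are likely to share influences.

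The main claim is at stake. The abstract says that the study will test prevention or delay of non-communicable disease, and the Discussion makes the intervention-control comparison the primary aim.

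**Working it through.** **Inputs from the protocol article.** 5630 people in one intervention centre, 9375 in two control centres, 30% attrition (Sample size).

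**Assumptions.** The article gives no centre-level ICC, so a range is used for ρ, the ICC of the outcome or of its change. The two control centres are taken as equal in size; unequal sizes would raise the error. Family correlation is left out.

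**The plan's own figure.** The intervention sample size of 4750 cannot be reproduced, because the article gives no cholesterol mean or SD and no phase 2 alpha or power. The point does not depend on it. The stated 5% design effect, read as 1.05, offers no cover: with a cluster of 5630 it implies ρ = 0.05/5629 ≈ 0.000009, whereas ρ = 0.001 would give 1 + 5629 × 0.001 ≈ 6.6. It also enters only the sample size, not the tests.

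**Step 1, individual-level standard error.** After attrition: 5630 × 0.7 = 3941 and 9375 × 0.7 ≈ 6563. Variance of the difference in SD² units: 1/3941 + 1/6563 = 0.000406, so SE = 0.0202 SD.

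**Step 2, add centre variation.** One centre against the mean of two contributes ρ(1 + 1/4 + 1/4) = 1.5ρ. The true variance is (1 − ρ) × 0.000406 + 1.5ρ.

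**Step 3, actual error of the nominal two-sided 5% test.** 2[1 − Φ(1.96 × naive SE / true SE)].

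| Assumed ρ | True SE (SD) | Variance ratio | Type I error | 95% half-width, 1.96 × true SE (SD) |
|---|---|---|---|---|
| 0 | 0.0202 | 1.00 | 5% | 0.039 |
| 0.00005 | 0.0219 | 1.18 | 7% | 0.043 |
| 0.0001 | 0.0236 | 1.37 | 9% | 0.046 |
| 0.0005 | 0.0340 | 2.85 | 24% | 0.067 |
| 0.001 | 0.0437 | 4.69 | 37% | 0.086 |
| 0.005 | 0.0889 | 19.5 | 66% | 0.174 |

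Without attrition the last three type I errors are 30%, 43% and 71%. More people make the problem worse, because the naive SE shrinks while the 1.5ρ term stays.

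**Step 4, can the centres themselves supply a test?** Hardly. Three centres leave 1 degree of freedom (critical t = 12.7), and a permutation of one centre out of three cannot give p below 1/3. One might instead claim an effect whenever the intervention centre differs from both controls by more than they differ from each other. With no effect, simulation with the numbers above meets that condition 32% of the time at ρ = 0 and 33% at ρ = 0.0005 to 0.005. It cannot serve as a claim rule.

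**The case against.** - **The size is conditional.** No centre ICC is documented, least of all for change scores within one city district. At 0.00005 to 0.0001 the error is only 7% to 9%. This stands: the table is an illustration. A reader might infer that the trial's error rate is known to be 24% to 66%; the article does not support that.
- **The plan does more than t and chi-square tests.** It includes age- and sex-adjusted incidence, multi-way ANOVA, ANCOVA, Mantel-Haenszel, paired and repeated-measures comparisons with baseline, and Cox regression. So a reader should not infer that every centre difference will be read as an effect without adjustment. Measured covariates can be handled. The centre effect itself cannot, because it is fully aliased with the intervention.
- **Family correlation is mentioned.** A reader might infer that the plan ignores family clustering. The sentence that sets the individual as the unit goes on to promise intraclass correlations for relations within families. Whether that covers the intervention-control tests is unclear, so this is a secondary point of wording.
- **Random selection is stated.** It describes how centres and people were sampled into the study. The article does not claim random allocation to arms, and it should not be charged with doing so.
- **The groups look alike at baseline.** Largely so, but similar baseline means do not secure similar trends. Table 3 also shows gaps: literacy at 70 and over is 44.1% in control and 59.5% in intervention; employment at 50–59 is 37.1% and 26.9%.
- **The design has been in the field since January 2002.** True, and no model repairs one intervention cluster. What remains open is the analysis and its interpretation.

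**Conclusion.** The point holds. It concerns what the article fixes (unit of analysis and named tests), not something left to a fuller plan, and it conflicts with the article's own statement that "each health center in district 13 was a cluster". The direction is certain for any positive centre-level ICC: the stated p-values are too small and the intervals too narrow. The size is not known from the article. Under the assumptions above it runs from slight (7% at ICC 0.00005) to severe (66% at 0.005). The finding rests on the centre level alone and does not need family clustering to be ignored.

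**What to change.** 1. State that the intervention-control comparison is a non-randomised comparison of one centre with two, and that individual-level p-values alone are not evidence of an intervention effect.
2. Make the main analysis the change from phase I, reported separately for each of the three centres. State that family clustering is accounted for in all intervention-control comparisons. This step alone still leaves centre-level variation out of the standard error, so step 4 is needed.
3. Report control centre against control centre from the same model, as a descriptive yardstick of between-centre variation and not as a rule for claiming an effect.
4. Give the main intervention-control interval with 1.5ρ (times the outcome variance) added to its variance, over a stated range of centre ICCs such as 0 to 0.005, and word the conclusions to match.

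This changes analysis and wording only and needs no new data. The cost is wider intervals and more cautious claims: in the illustration the half-width grows from 0.039 to 0.174 SD across that range. The single intervention cluster remains a limit that no analysis fully removes.

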### Physical activity levels

Physical activity level was assessed using Lipid Research Clinic (LRC) questionnaire [25] in the first phase of the TLGS. Since the LRC questionnaire assesses physical activity level of the participant qualitatively and the questions are fully subjective, the derived data were not accurate. So, the Steering Committee of the TLGS replaced the questionnaire by Modifiable Activity Questionnaire (MAQ) [26] and a Persian translated form of that is used to assess physical activity level in the TLGS participants. The questionnaire measures all three forms of activities including leisure time, job, and household activities in the past year.

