### Lifestyle interventions

Interventions are aimed at lifestyle modification through primary, secondary and tertiary preventions for NCD by improving nutrition and dietary pattern, increasing physical activity levels, and smoking cessation. Training sessions for coping with the stress for families, and life skills training for schoolchildren are also performed. A total of 5630 people from district No. 13 were chosen for interventions. The rationale for choosing this area was that the population residing in district No. 13 is stable, medical and health facilities in this district are under the administration of Shahid Beheshti University of Medical Sciences and the intervention area is far away from control areas.

Demographic characteristics of both intervention and control groups are shown in Table 3. Mean age was 34.0 ± 19.2 and 33.0 ± 18.8 years and mean BMI was 24.4 ± 5.9 and 24.2 ± 5.9 kg/m^2 ^and the prevalence of literacy was 92.3 and 92.6% in intervention and control groups, respectively. It is noteworthy that all participants speak Persian and there is no language barrier. There are only 7.5% illiterate people. All others could read and understand materials which are provided for education. The illiterate individuals are older than 50 and are educated face-to-face by staff and other family members.

**Table 3 T3:** Baseline characteristics of the intervention and control subjects

Age Group (years)	Characteristics	Control	Intervention	P Value
3–9	Male(%)	48.9	49.2	0.90
	Literate (%)*	80.1	79.0	0.69
	Mean age (Year)	6.4	6.4	0.54
	Daily Cigarette smoker (%)	0	0	-----
	Mean body mass index (kg/m2)	15.42	15.7	0.13
				
10–19	Male(%)	46.3	48.8	0.16
	Literate (%)	99.8	99.8	0.65
	Employed (%)	1.8	2.1	0.62
	Marital status (Married %)	1.5	2.1	0.25
	Mean age (Year)	14.5	14.6	0.27
	Daily Cigarette smoker (%)	1.5	2.4	0.12
	Mean body mass index (kg/m2)	20.2	20.1	0.45
				
20–29	Male(%)	38.9	35.5	0.10
	Literate (%)	99.7	99.8	0.83
	Employed (%)	30.8	32.5	0.40
	Marital status (Married %)	48.4	51.3	0.12
	Mean age (Year)	24.3	24.4	0.29
	Daily Cigarette smoker (%)	6.7	7.5	0.06
	Mean body mass index (kg/m2)	24.2	24.3	0.87
				
30–39	Male(%)	43.1	41.8	0.50
	Literate (%)	99.5	98.7	< 0.05
	Employed (%)	50.3	50.0	0.86
	Marital status (Married %)	90	86.0	< 0.05
	Mean age (Year)	34.4	34.4	0.44
	Daily Cigarette smoker (%)	15.5	15.1	0.40
	Mean body mass index (kg/m2)	26.5	26.8	0.16
				
40–49	Male(%)	40.5	42.8	0.32
	Literate (%)	96.3	96.1	0.79
	Employed (%)	45.2	46.0	0.74

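### In a non-randomised comparison of one health centre with two, adjustment is optional and the outcome's own phase I value is never fixed as a covariate

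*Protocol article*

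**What the plan says.** All references are to the protocol article.

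**Allocation.** Under Sample size: "population covered by one of the 3 health centers (5630 people) selected for intervention and 9375 subjects under coverage of other two centers used as" (the comparison group). The text with Figure 1 describes the intervention group as those "under coverage of one of the three health centers which is far from two other centers", and Lifestyle interventions gives as one reason that "the intervention area is far away from control areas". Distance and administration decided the groups, not chance.

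**Between-group tests.** Under Biostatistical considerations: "Continuous variables will be compared between intervention and control groups using" Student's t-test. Proportions get Chi-square or Fisher exact tests.

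**Adjustment.** The same paragraph continues: "To adjust the comparison by the potential confounding variables, two or three-way ANOVA will be used". It adds analysis of covariance for use with a covariate related to the outcome, and Mantel-Haenszel for proportions where adjustment is needed. Incidence is to be adjusted mainly for age and sex. Logistic and Cox models are listed for relating risk factors to outcomes.

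**Comparison with baseline.** "To compare the data with their baseline, paired t-test and repeated measures analysis of variance or McNemar, Sign and Friedman tests will be used". No group-by-time term is stated.

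**Baseline.** "Mean age was 34.0 ± 19.2 and 33.0 ± 18.8 years" in the intervention and control groups respectively; mean BMI is 24.4 and 24.2, each with SD 5.9. Table 3 gives further characteristics by age band.

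**Physical activity.** Of the phase I questionnaire, which was later replaced: "the derived data were not accurate".

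**The concern.** When groups are formed by place, a raw difference at follow-up mixes any intervention effect with whatever already separated the areas. Adjustment is then a standing requirement, and the strongest single covariate is usually the person's own earlier value of the outcome. Phase I collected this for lipids, fasting glucose, blood pressure and body size, yet the article names a raw t-test as the group comparison and leaves adjustment to circumstances. ANOVA on categorical factors does not carry a continuous baseline value, and the sentence on covariance analysis does not mention one.

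The within-group tests are a second route to a misleading statement. The nutrition clinics take people because they have dyslipidaemia, hypertension, diabetes or excess weight. In people picked for high values, some fall is expected without any intervention.

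At stake is the primary research goal, the effectiveness of the lifestyle programme.

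**Working it through.** **The plan's own figure.** The intervention-group size of 4750 is the only figure tied to this comparison, and it is not disputed here. It cannot be reproduced, because the article gives no cholesterol mean, SD or phase II power. Only its 5% cholesterol effect and 30% attrition are used below.

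**1. Baseline gaps (inputs from Lifestyle interventions; n = 5630 and 9375).**
- Age: z = (34.0 − 33.0) / √(19.2²/5630 + 18.8²/9375) = 1.0/0.3212 = 3.11, p = 0.002. The gap is about 0.05 SD.
- BMI: z = (24.4 − 24.2) / √(5.9²/5630 + 5.9²/9375) = 0.2/0.0995 = 2.01, p = 0.044. The gap is 0.2/5.9 = 0.034 SD. The means are rounded to 0.1, so the true difference of means lies between 0.1 and 0.3, and p between 0.31 and 0.003.
- Both tests treat people as independent. Whole families were recruited, so the evidence is weaker than these p-values suggest.
- Table 3, control vs intervention: literacy at 70 and over 44.1% vs 59.5% (p < 0.001); employment at 50–59 37.1% vs 26.9% (p < 0.05).
- Table 3 shows no lipid, glucose or blood pressure values by group, so imbalance in those outcomes cannot be judged from the article.

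**2. What a small imbalance does to a follow-up-only t-test.** Let D be the true gap in the outcome at phase I in SD units, and ρ the baseline-to-follow-up correlation (assumed 0.5 to 0.8). After 30% attrition, n = 3941 and 6562.5, and SE = √(1/3941 + 1/6562.5) = 0.0202 SD. With no intervention effect, and with the gap shrinking in proportion to ρ, the bias is ρD. The rejection rate at two-sided 5% is then:

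| D (SD) | ρ | bias ρD | bias/SE | rejection rate |
|---|---|---|---|---|
| 0.05 | 0.5 | 0.025 | 1.24 | 24% |
| 0.05 | 0.8 | 0.040 | 1.98 | 51% |
| 0.034 (observed BMI gap) | 0.5 | 0.017 | 0.84 | 13% |
| 0.034 (observed BMI gap) | 0.8 | 0.027 | 1.35 | 27% |

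The bias itself is small. At an assumed cholesterol SD of 45 mg/dl, 0.040 SD is 1.8 mg/dl, against a planned 5% of an assumed mean of 200, which is 10 mg/dl. The danger is false significance rather than a false effect of the planned size.

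**3. Baseline adjustment and difference in change are not the same estimate.** If the gap shrinks in proportion to ρ, the baseline-adjusted model is unbiased and the change score is biased by −(1 − ρ)D. If the areas differ by a constant D at both times, the change score is unbiased and the adjusted model is biased by (1 − ρ)D, which is 0.010 to 0.025 SD for D = 0.05. The follow-up-only difference is biased in both cases (by ρD or by D).

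**4. Regression to the mean in people selected at 240 mg/dl or more** (the article's high-risk cut-off; mean, SD and ρ are assumed). The selected mean is M = μ + σφ(a)/Q(a), with a = (240 − μ)/σ. The expected untreated fall is (1 − ρ)(M − μ).
- μ = 200, σ = 45: M = 264.7. The fall is 12.9 mg/dl (4.9%) at ρ = 0.8 and 32.3 mg/dl (12.2%) at ρ = 0.5.
- μ = 210, σ = 45: M = 266.9. The fall is 11.4 mg/dl (4.3%) at ρ = 0.8 and 28.5 mg/dl (10.7%) at ρ = 0.5.

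The range is about 4% to 12%, against a planned effect of 5%. It applies only to before-after tests in selected people.

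**The case against.** The strongest reply is that the article does plan adjustment. The t-test sentence is followed at once by two- or three-way ANOVA, covariance analysis and Mantel-Haenszel. A phase I value is a covariate related to the outcome, so the text already permits what is asked for. A reader who stops at the t-test might infer that the whole comparison rests on unadjusted tests; the document does not support that. Nor would a missing covariate list be a finding by itself, since an article may leave it to the full plan. What remains is what the article does state: a raw test as the group comparison in a non-randomised design, with adjustment conditional.

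A reader might also infer that regression to the mean distorts the main comparison. It does not. The abstract and the Discussion (Target groups and aims) describe an intervention population set against a concurrent control population, and in unselected people there is no net shift. The article nowhere says that effectiveness will be judged from uncontrolled before-after tests. It lists such tests and does not limit their use.

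The imbalance evidence is modest, and this part of the objection stands. The gaps are about 0.05 and 0.03 SD, and family clustering is ignored. Table 3 has 53 tested rows, so two or three would fall below 0.05 by chance (53 × 0.05 = 2.65); four clearly do. Table 3 tests age only within bands, but the accompanying text gives the overall means, so nothing is concealed.

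Finally, no change score across the two physical-activity questionnaires is announced. That is so; the general rule for comparison with baseline simply makes no exception for it.

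**Conclusion.** The point holds in a limited form. The article lists adequate tools but does not commit to them. An unadjusted follow-up difference or a within-group test could be presented as the intervention effect without departing from the text. The documented imbalances are small. A 0.05 SD imbalance in an outcome is still enough for a spurious significant result in 24% to 51% of cases, assuming correlations of 0.5 to 0.8, 30% attrition and independent individuals. The matching bias is well below the planned 5% cholesterol effect. The 4% to 12% regression-to-the-mean range rests on an assumed cholesterol mean, SD and correlation, and concerns selected subgroups only.

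A reader might take baseline adjustment to make the comparison causal. It would not: with one intervention centre against two, differences between centres remain confounded with the programme whatever is measured on individuals.

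**What to change.** In Biostatistical considerations:

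- **Continuous outcomes.** Make the main effect estimate a between-group model of the follow-up value on group, the person's own phase I value, age and sex, adding education (Table 3 records literacy) and employment in adults. Report the between-group difference in change as a sensitivity analysis, and discuss any disagreement between the two.
- **Binary outcomes.** Use the analogous adjusted model in place of a bare Chi-square or Fisher test.
- **Within-group tests.** Keep paired t, McNemar, Sign and Friedman tests as description only, and draw no conclusion on effectiveness from them. If repeated measures ANOVA is used for effectiveness, state the group-by-time contrast.
- **Physical activity.** Compute no change from phase I, because the instrument was replaced. Compare the new questionnaire's scores between groups.
- **Limitation.** State that person-level adjustment does not remove confounding between centres.

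The cost is analysis wording. The core covariates are already recorded, so no new data collection is needed. Where phase I measured an outcome in only part of the sample (for example, diet in one tenth of families), the baseline-adjusted model applies to that part only.
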